## Abstract

**Introduction:**

High-intensity interval training (HIIT) is an emerging method of cardiac rehabilitation, which is more and more popular in recent years. Research into the effect of HIIT on peak oxygen uptake (VO_2_ peak) and myocardial fibrosis among patients with myocardial infarction (MI) is lacking. Here, we describe the rationale along with the protocol for a clinical trial to test the following hypotheses: (1) compared with the control group, VO_2_ peak will be increased in both the moderate-intensity continuous training (MICT) and HIIT groups and (2) compared with the control group, myocardial fibrosis due to MI will be improved by HIIT and MICT.

**Methods and Analysis:**

This is a single-center, randomized controlled clinical trial. In total, 180 patients with MI are to be recruited for this study. VO_2_ peak will be tested by cardiopulmonary exercise testing (CPET) and myocardial fibrosis will be evaluated by cardiac MR. A variety of blood and psychometric tests and also the peripheral arterial tonometry, reactive hyperemia index for microvascular endothelial function, and microvascular blockage or digital vasomotor response are included.

**Ethics and Dissemination:**

The ethics committee of the Guangdong Provincial People's Hospital has authorized this mechanistic clinical research. Peer-reviewed articles and conference presentations will be used to disseminate the findings.

**Trial Registration Number:**

NCT04863677.

## Introduction

More than 7 million people suffer from acute myocardial infarction (AMI) worldwide each year (1). And in the past decades, more and more numbers of research have shown significant reductions in AMI mortality with more effective treatment (1, 2). Despite the decreasing mortality after the first myocardial infarction (MI), 20% of MI survivors have a second cardiovascular event in the first year after MI onset (3). More sufficient and effective post-MI rehabilitation methods are in need to reduce the occurrence of adverse events.

Numerous investigations have documented that cardiac rehabilitation (CR) will prolong the survival time of patients with MI, decrease the risk of readmission and enhance the quality of life (4–6). Multidisciplinary exercise-based CR is recommended for individuals with coronary artery disease for maintaining a healthy lifestyle and regulating risk factors to reduce all-cause along with cardiovascular mortality, and morbidity and improve health-related quality of life (Class I, Level A) (7–10). India's study enrolled 3,959 patients with acute MI. The subjects were assigned at random into either the Yoga-CR program (*n* = 1,970) or improved conventional treatment with educational counseling (*n* = 1,989). The researchers found the Yoga-CR group had a greater return to preinfarct (11), short-term cardiac rehabilitation after MI did not increase survival, psychological wellbeing, or health-linked quality of life in the long run, according to a randomized controlled experiment (Rehabilitation After Myocardial Infarction Trial) by Barry A (12). Given the inconsistent results of previous studies, it is necessary to reassess the effects of different forms of exercise training for patients with MI. Peak oxygen uptake (VO_2_peak) is the gold standard for determining functional limitations and the integrative physiology of the circulatory, respiratory, muscular, cellular, and oxidative systems (13, 14). Exercise therapy, as the core of CR, improves VO_2_peak. With the increment of VO_2_ peak by 1 ml·kg^−1^·min^−1^, death risk in individuals with coronary heart disease (CHD) decreases by 15% (9). VO_2_ peak is, likewise, a remarkable individual predictor of mortality and morbidity (15, 16). The purpose of this study is to clarify the effect of two different training methods on VO_2_ peak in patients with MI. High-intensity interval training (HIIT) is defined by repeated high-intensity movements, interspersed with low-intensity recovery periods. Moderate-intensity continuous training (MICT) improves endurance mainly, demonstrating an inferior effect on VO_2_ peak compared with HIIT (17). Despite evidence that HIIT raises VO_2_ peak more than MICT, the reasons behind this advantage remain unknown. Given prior data, it is unknown if HIIT results in a greater increase in cardiac output than MICT. In comparison to MICT, HIIT seems to stimulate more genes involved in the control of mitochondrial biogenesis and oxidative enzymes in skeletal muscle (18). In addition, HIIT was shown to decrease the left ventricle's peak apical rotation and torsion (19). The energy required for myocardial contraction to meet daily workload may be reduced as a result of the reduction in peak left ventricular torsion generated by HIIT. In addition, HIIT decreased the time required to achieve the peak value of the left ventricle (19). Dun et al. (20) discovered that supervised HIIT may result in a substantial reduction in total fat mass and abdominal fat percentage, and an improved lipid profile, in patients undergoing CR who had MI. They also indicated that supervised HIIT, compared to MICT, resulted in remarkable improvements in metabolic syndrome and body composition in individuals with MI (21). It is worth further investigation to compare the effects of the two different exercise training programs in patients with MI.

Following MI, cardiomyocyte necrosis initiates an inflammatory cascade that clears the wound of dead cells, induces collagen production, activates myocardial fiber cells, and retains the ventricle's structural integrity (22). When myocardial fibrosis continues to develop, myocardial contractility and coronary flow reserve both decrease eventually leading to malignant arrhythmia and cardiac death (23). Thus, preventing and reversing myocardial fibrosis is a critical component of the postinfarction approach. Alemasi et al. (24) hypothesized that exercise training protects the myocardium against isoproterenol-induced fibrosis and diastolic dysfunction by suppressing cytokines in the Hedgehog and RAP1 pathways. However, another study used cardiac magnetic resonance (CMR) to detect myocardial fibrosis in asymptomatic triathlon athletes, showed that among 54 male triathlon athletes, there are 9 players (17%) having myocardial fibrosis, which shows that excessive physical training can lead to the occurrence of myocardial fibrosis (25).

Cardiac magnetic resonance (CMR) is a non-invasive method for evaluating CHD. It is the gold standard technique for assessing myocardial fibrosis and cardiac function, and scarred myocardium in patients with MI (26). Edema, an important character of myocardial impairment in the process of acute MI (27), will affect CMR assessment of myocardial fibrosis. There was no change in swelling for the first week; however, after 15 days the amount of edema dropped dramatically (27). A larger peak in myofibroblast surface area seven days after MI was seen in a rat experiment in which researchers discovered that myofibroblasts were present for up to 14 days in a ligated MI model (28). According to the relation in ages of laboratory rats with humans (29), in this study, we will enroll patients 6 weeks to 3 months after MI, evaluate myocardial fibrosis by CMR at baseline and 3 months after exercise training, to explore the effect of different exercise program on myocardial fibrosis.

The main objective of the study is to explore the effect of HIIT, MICT, and guideline-based physical activity on VO_2_peak and myocardial fibrosis in patients with MI. The secondary objective is to assess the effect of HIIT, MICT, and guideline-based physical activity on endothelial function, body mass index (BMI), arrhythmias, and inflammatory markers.

## Methods and Analysis

### Study Design

This study is now being carried out at the Guangdong Provincial People's Hospital in Guangzhou, Guangdong, China. The research methodology and procedures (No. GDREC2020208H(R1)) were approved by the ethics committee of the Guangdong Provincial People's Hospital.

The HIIT on MI study is an ongoing randomized controlled trial (RCT), followed up with a 1-year observing period. The first patient was recruited on April 2021. This study is to be completed by March 2024. After completing a written permission form, patients are evaluated to see whether they are eligible.

A 12-week cardiac rehabilitation training program (HIIT, MICT, and guideline-based physical activity) will be studied to determine the impact of HIIT and MICT on VO_2_peak, cardiac fibrosis, endothelial function, microvascular obstruction, arrhythmia, body fat, inflammation, and psychological effects on participants. The schematic design of the study is shown in Figure 1.

**Figure 1 F1:**
[figure not shown]
The process of study.

### Inclusion Criteria

(1) Age range: 18 to 75 years.

(2) Individuals with AMI who were treated with revascularization 6–12 weeks after the beginning of the AMI and harbored a New York Heart Association functional classification (NYHA) Class I–III; (AMI verified *via* the Fourth Universal Definition of Myocardial Infarction). The term “acute myocardial infarction” must be utilized when there is medical evidence of acute myocardial ischemia along with a detection of a fall and/or rise in cTn values with manifestations of myocardial ischemia; new alterations in ischemic ECG; developing pathological Q waves; images exhibiting prove of new loss of viable myocardium or new abnormality of regional wall motion in a pattern congruent with an ischemic etiology; and determination of a coronary (not for type 2 or 3 MIs).

(3) Able and willing to finish the CR program independently, as determined by the informed consent form.

(4) Complete cardiopulmonary exercise testing (CPET) during enrollment or within 1 month of receiving the CPET result.

### Exclusion Criteria

(1) onduct high-intensity exercise regularly.

(2) Currently enrolling in any other clinical trials.

(3) Have any other significant health condition in the preceding year (e.g., severe valvular disease, congenital heart disease, recurrent ventricular arrhythmias, NYHA Class IV heart failure, atrial fibrillation, cancers, and end-stage renal or liver disease).

(4) Dementia; infirmity; or inability to participate in sports (musculoskeletal limitations, namely, injuries, frailty, and weakness).

(5) Acute liver failure with severe complications.

(6) Acute renal failure with severe obstructive nephropathy.

(7) Irregular vital signs: heart rate at rest <40 or > 120 bpm, or blood pressure: systolic blood pressure > 200 mm Hg, diastolic pressure > 110 mm Hg, *T* ≥ 38.5 or ≤ 36°C, SpO_2_ ≤ 90%.

(8) Inspectors at the site determine that the patient will be unable to finish the trial and/or attend follow-up.

If the patient has ischemic performance during exercise, such as chest pain and chest tightness, immediately stop exercise, and re-evaluate. According to the assessment of professional cardiologists, if surgery is needed, surgical treatment will be carried out, and such patients will withdraw from the study. If it can be relieved after rest, a new exercise plan will be re-established.

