### Sample Estimation

Based on the degree of myocardial fibrosis at the primary endpoint, the sample size was estimated using G Power3.1.9.4, one-way ANOVA, and *a priori* followed by an *F* test was performed. Since there is no previous reference for similar research data, the effect size of the observable indicator in this study is set to be 0.25. To achieve more than 80% power and a 2-sided critical threshold of 0.05, each arm must contain a minimum of 53 patients. Estimating a 10% loss to follow-up, the recruitment goal is 60 patients per arm (*n* = 180).

As for VO_2_ peak, based on our pre-experiment, the mean increase of peakVO_2_ in control, MICT, and HIIT groups after exercise training is −0.18, 2.86, and −0.36 ml/kg/min, and the standard deviation of the difference between groups is 2.92, 3.38, and 2.74. By one-way ANOVA *F*-tests, sample sizes of 18, 18, and 18 are obtained from the 3 groups whose means are compared. The total sample of 54 subjects achieves 80% power to detect differences among the means of peakVO_2_ using an *F*-test with a 0.05 significance level. Estimating a 10% loss to follow-up, the recruitment goal is 20 patients per arm (*n* = 60).

Taking two primary endpoints together, the recruitment goal is 60 subjects per arm.

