### Study Procedures

Supervised exercise training will be performed 3 times per week at the CR center in the Guangdong Provincial People's Hospital. All patients are assigned at random in a 1:1:1 ratio to one of three groups: HIIT (group 1), MICT (group 2), or control group (group 3). This program consists of 36 CR sessions and typically lasts 12 weeks (3 sessions per week).

All patients receive drug treatment after MI, routine health education, and postoperative medication guidance according to the guidelines. The control group receives no extra rehabilitation or physical activity. Patients in the groups 1 and 2 perform MICT during the first week of CR, after which, they will enter the corresponding group according to the random number of the entry period.

Exercise intensity is personalized based on the results of CPET. During CPET, patients try their best to obtain peakVO_2_ data. According to the percentage of peakVO_2_ to design exercise training programs: high strength refers to 85 to 100% peak VO_2_ and 85% peak VO_2_ is higher than the anaerobic threshold (AT); medium intensity: 40 to 60% peak VO_2_, and 60% peak VO_2_ is less than AT; and low intensity means 20% peak VO_2_. The exercise intensity also could be micro-adjusted according to the rating of perceived exertion (RPE) during the actual cardiac rehabilitation exercise. Short bursts of high-intensity exercise are alternated with intervals of low-intensity activity in HIIT programs (active recovery). HIIT constitutes twenty intervals of high effort (30–60 s at an RPE (Borg scale of 6–20) of 15–17) along with a low intensity (1 min at an RPE (Borg scale of 6–20) of 10 or completely rest). It takes about 40–50 min to complete the entire training cycle (Figure 2). Patients in the MICT group exercise for 40–50 min at an RPE of 12 to 14 (four sets of 5–8 min each, with a 2-min rest in between) (Figure 3). HIIT and MICT are only done under supervision once a week on a non-consecutive 3-day schedule. A professional CR team also keeps an eye on all of the patients. Clients may also participate in 3 days of home-based exercises guided by a sports wristband after being evaluated by therapists and physicians.

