### Primary and Secondary Outcomes

Primary outcomes: changes in VO_2_ peak after 12 weeks of exercise training in the three groups (HIIT group, MICT group, and control group), and changes in myocardial fibrosis in the three groups.

Secondary outcomes: changes in ST-2, endothelial function, microvascular obstruction, body fat, BMI, the incidence of arrhythmia, and quality of life in three groups after 3 months.

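### Patients whose ischaemia during exercise leads to surgery leave the study, not just the training; this loss is likely to fall mainly on the exercise arms and can bias both primary comparisons

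*Protocol article*

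**What the plan says.** The rule is in the closing paragraph of Exclusion Criteria. It opens with "If the patient has ischemic performance during exercise, such as chest pain and chest tightness, immediately stop exercise, and re-evaluate". If cardiologists then judge an operation necessary, "if surgery is needed, surgical treatment will be carried out, and such patients will withdraw from the study". Otherwise, "If it can be relieved after rest, a new exercise plan will be re-established".

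Study Procedures describes 36 sessions over 12 weeks for the exercise programme and says of the third arm: "The control group receives no extra rehabilitation or physical activity". Study Design words it differently: "A 12-week cardiac rehabilitation training program (HIIT, MICT, and guideline-based physical activity) will be studied". The objectives at the end of the Introduction also name guideline-based physical activity as the third condition.

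Primary and Secondary Outcomes makes the 12-week change in VO2 peak and the change in myocardial fibrosis co-primary. Under Cardiac MR, fibrosis is imaged at baseline and at month 3. Sample Estimation handles loss only as a count: "Estimating a 10% loss to follow-up, the recruitment goal is 60 patients per arm".

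**The concern.** The paragraph sits among the eligibility criteria, but it is not only a screening rule. A plan can be re-established only for someone who already had one, so the rule reaches patients already randomised and training. It takes them out of the study, not merely out of the exercise sessions.

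Three features together make this a statistical matter:

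- **The trigger depends on the arm.** Ischaemia during exercise is more likely to be seen where the trial supplies exercise. On the Study Procedures text, that is two arms of three. HIIT and MICT also differ in intensity, so the trigger may differ between them too.
- **The event is related to prognosis.** Patients who need an operation for ischaemia are unlikely to be a random sample of their arm.
- **The outcome is lost.** Anyone who leaves before month 3 has neither primary outcome. Comparable control patients, not provoked by training, stay and are measured.

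At stake is the protection that randomisation gives to HIIT versus control, MICT versus control and, if the rates differ, HIIT versus MICT.

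**Working it through.** **1. The plan's own figures.** For fibrosis, Sample Estimation gives a three-group one-way ANOVA with f = 0.25, alpha 0.05 and power above 80%. With noncentrality N·f², 53 per arm gives power 0.805 and 52 gives 0.797, so the stated 53 is reproduced. Inflating, 53 / 0.9 = 58.9, or 59; the plan recruits 60. The room for loss is 60 − 53 = 7 per arm. For VO2 peak the plan needs 18 per arm, and 18 / 0.9 = 20 as stated. Recruiting 60 therefore leaves ample numbers for that endpoint.

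This allowance concerns numbers only. It assumes that those lost resemble those who stay, or at least that they differ equally in every arm.

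**2. Bias in an arm mean.** Let q be the share of an exercise arm withdrawn, C the mean change among those who stay, and C − D the mean change the withdrawn would have shown. The mean for everyone randomised is (1 − q)·C + q·(C − D) = C − q·D. If only those who stay are measured, the arm mean is off by q·D.

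The documents give neither q nor D. Assumed ranges: q from 1% to 10% (0.6 to 6 of 60) and D from 1 to 5 ml/kg/min.

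| q | patients of 60 | shift at D = 1 | shift at D = 5 |
|---|---|---|---|
| 1% | 0.6 | 0.01 | 0.05 |
| 2% | 1.2 | 0.02 | 0.10 |
| 5% | 3 | 0.05 | 0.25 |
| 10% | 6 | 0.10 | 0.50 |

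(Shifts in ml/kg/min.) For scale, the pilot MICT-minus-control difference in Sample Estimation is 2.86 − (−0.18) = 3.04 ml/kg/min. The largest shift is 0.50 / 3.04 = 16% of that, and the smallest is 0.01 / 3.04 = 0.3%.

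**3. Effect on the F test.** Suppose there is no true difference, 60 controls are all measured, the same share q is lost from both exercise arms, and D is expressed in SD units. The noncentral F distribution gives these true type I errors for a nominal 0.05:

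| q | exercise n per arm | D = 0.5 SD | D = 1 SD | D = 1.5 SD |
|---|---|---|---|---|
| 2% | 59 | 0.050 | 0.051 | 0.053 |
| 5% | 57 | 0.052 | 0.057 | 0.067 |
| 10% | 54 | 0.057 | 0.080 | 0.120 |

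For VO2 peak, 1 SD is about 3.03 ml/kg/min: √((2.92² + 3.38² + 2.74²) / 3). In SD units the table applies equally to fibrosis, for which the plan gives no SD.

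**4. Numbers against bias.** At q = 10% each exercise arm keeps 54 patients, still above 53. The sample-size target would be met while the type I error stood at 0.080 for a 1-SD gap. Meeting the target is therefore no reassurance on this point.

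**The case against.** The strongest reply is that the effect may be tiny. Everyone enrolled has been revascularised (Inclusion Criteria) and has a symptom-limited maximal exercise test before training (Cardiopulmonary Exercise Testing), so many patients with inducible ischaemia may be found beforehand. At 2% withdrawn, the shift is at most 0.10 ml/kg/min and the type I error barely moves. This stands: the documents do not show that the rate is high.

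Several stronger readings are tempting, and the text does not carry them:

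- **That the rule operates almost exclusively in the exercise arms.** Study Procedures points that way, but the Introduction and Study Design give the third arm guideline-based activity, the rule speaks of exercise generally rather than trial sessions, and all arms may be exercise-tested. "Mainly" is a fair inference; "almost only" is not.
- **That the comparison is certainly biased in favour of exercise.** Those withdrawn are not documented to be the poorest responders, and surgery may itself change VO2 peak and the CMR findings. The direction is plausible, not established.
- **That harm is concealed.** Nothing says these withdrawals will go uncounted. Safety reporting by arm, analysis sets and sensitivity analyses are commonly left to a full protocol or SAP, neither of which is shown.
- **That the shift is large.** The upper figure of 0.5 ml/kg/min pairs two assumed extremes.

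One part of the reply fails. An unseen SAP can define analysis sets and missing-data methods, but it cannot recover month-3 measurements that were never taken because the patient had left under a stated rule.

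**Conclusion.** The point holds in a limited form. As written, the rule creates a post-randomisation, prognosis-related loss of both primary outcomes that is likely to fall mainly on HIIT and MICT and **can** bias the VO2 peak and fibrosis comparisons. Under the assumed 1–10% withdrawn and 1–5 ml/kg/min gap, the shift in an exercise-arm mean is about 0.01–0.5 ml/kg/min: negligible to small at 1–2% withdrawn, moderate at 10%.

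These ranges are assumptions, and no figure in the protocol narrows them. The conclusion also rests on trial training being confined to two arms, on which the protocol is not consistent. The case for acting is not a demonstrated large bias: the exposure is avoidable at little cost, and data not collected cannot be retrieved later.

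**What to change.** Leave the clinical decision, including whether and when to operate, exactly as it is. Change only the research consequence:

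- Replace withdrawal from the study with the end of trial training while the patient remains in follow-up.
- Obtain the month-3 CPET, CMR, ECG and SF-36 where medically permitted.
- Analyse these patients in their randomised arm, with surgery recorded as an intercurrent event.
- Reconcile the descriptions of the control arm in the Introduction, Study Design and Study Procedures, so that exposure to the trigger in each arm is clear.

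The cost is a change of wording and a few month-3 visits that are already planned; the recruitment target does not change. The downside is slightly more heterogeneous outcomes, because some retained patients will have had surgery. Some will also be unfit for a month-3 test, so the bias is reduced rather than wholly removed.

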### Sample Estimation

Based on the degree of myocardial fibrosis at the primary endpoint, the sample size was estimated using G Power3.1.9.4, one-way ANOVA, and *a priori* followed by an *F* test was performed. Since there is no previous reference for similar research data, the effect size of the observable indicator in this study is set to be 0.25. To achieve more than 80% power and a 2-sided critical threshold of 0.05, each arm must contain a minimum of 53 patients. Estimating a 10% loss to follow-up, the recruitment goal is 60 patients per arm (*n* = 180).

As for VO_2_ peak, based on our pre-experiment, the mean increase of peakVO_2_ in control, MICT, and HIIT groups after exercise training is −0.18, 2.86, and −0.36 ml/kg/min, and the standard deviation of the difference between groups is 2.92, 3.38, and 2.74. By one-way ANOVA *F*-tests, sample sizes of 18, 18, and 18 are obtained from the 3 groups whose means are compared. The total sample of 54 subjects achieves 80% power to detect differences among the means of peakVO_2_ using an *F*-test with a 0.05 significance level. Estimating a 10% loss to follow-up, the recruitment goal is 20 patients per arm (*n* = 60).

Taking two primary endpoints together, the recruitment goal is 60 subjects per arm.

